### 2.3 Number of subjects required

The primary outcome is defined as the proportion of students who improve their motivation to healthy sustainable food choices. By assuming a proportion of 5% in the control group (due to slight variation, independent of intervention), a type I error at 5% and a variation coefficient of cluster size of 50% (because class sizes can vary between 20 and 30), 36 clusters with 25 subjects in each group (control and intervention) allow to achieve 90% power to detect a difference between 5.0% and 11.5% in the proportion of students who improve their motivation to choose good food, by varying the intra-cluster correlation between 0.02 and 0.2. A 10% attrition effect was allowed for. To compensate for this loss, more classes were recruited for each area.

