#### 2.6.2 Control group

Classes assigned to the control group will not have access to Epidaure Market sessions before the end of the research evaluation. They will complete all three evaluation sessions (T0, T1 and T2). Depending on their teachers, control groups could benefit of Epidaure Market intervention and use the website after the T2 evaluation session.

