### 2.7 Outcomes

#### 2.7.1 Primary outcome measure

The intervention effectiveness will be assessed by comparing the proportion of students who improved their post-intervention parameters in the intervention and control groups. We chose motives for food choices because the intervention improves knowledge and motivation. Indeed, food choice motives are a key factor for changing towards sustainable behaviours [41–44, 46] and a measurement tool is available through a teen-friendly version of the questionnaire by Sautron and colleagues [62]. The questionnaire consists of 104 items divided into four categories: environmental, health and well-being, economic and miscellaneous (i.e. seasonal production, local production, etc.). The questionnaire used for this study had to be adapted to contain fewer items (28 items) and to fit in with the other questionnaires. The environmental, ethical, health and economic categories were included. All items are assessed with four-point Likert-type response scale, concerning their agreement with the stated sentence: 0-not at all agree; 1-strongly disagree; 2- quite agree; 3-strongly agree. A "don’t know" response is also possible if the student doesn’t know the word or concept evoked by the question. This questionnaire on food choice motivations is currently being validated. A factor analysis highlights a general factor: sustainable food, which will therefore be used as the primary outcome. Four secondary factors also emerge from the factor analysis and can be subdivided as follows: importance of ethics, environmental impact, locality and importance of health and absence of toxic substances. They can be used as outcomes in secondary analyses. Validation of the questionnaire will be the subject of another article.

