## 3. Data analysis plan

### 3.1 Analysis of quantitative data

As the sample is made of clusters (classes) that create a correlation between the individual measures, we will consider an analysis in two stages that will use as unit of analysis the cluster (class nested in the school).

For the primary outcome measure, a cross-sectional analysis using a mixed regression model with a random constant for the class effect. More specifically, a logistic regression model will be used on the dichotomous variables. We will also measure the associated intra-class correlation coefficients. A mixed linear regression model will be used for secondary analyses, when continuous variables are involved.

Finally, additional analyses will be carried out to verify the potential effect of socio-demographic characteristics, within the same area, and between the two areas.

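### Cutting the sustainable-food score into improved or not improved, with no stated T0 covariate, gives up roughly 40–64% of the information; a planned secondary model would keep it

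*Protocol article*

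**What the plan says.** Section 2.3 sizes the trial on a binary endpoint: "The primary outcome is defined as the proportion of students who improve their motivation to healthy sustainable food choices". Section 2.7.1 repeats it, with effectiveness assessed by "comparing the proportion of students who improved their post-intervention parameters in the intervention and control groups".

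The same section shows that a score lies underneath. The adapted questionnaire has 28 items with response codes 0 to 3, and "A factor analysis highlights a general factor: sustainable food, which will therefore be used as the primary outcome".

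Section 3.1 gives the primary model as "a cross-sectional analysis using a mixed regression model with a random constant for the class effect" and continues: "More specifically, a logistic regression model will be used on the dichotomous variables". The continuous route is present but ranked lower: "A mixed linear regression model will be used for secondary analyses, when continuous variables are involved". Section 3.1 names no T0 term for the primary model and excludes none.

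Sections 2.2 and 2.6.2 show that T0, T1 and T2 are collected, in control as well as intervention classes. Section 2.2 labels T1 as post-intervention, one month after the sessions. The article does not give the size of change that counts as improvement.

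**The concern.** A yes/no flag records only whether a student crossed a threshold. Where few students cross it, as with the 5% control rate in section 2.3, most of the movement in the score contributes nothing to the comparison. The flag also depends on the starting point: students near the top of the scale have little room to improve, and students who scored low by chance at T0 tend to rise. A T0 covariate would absorb much of that variation. Calling the analysis of a change-based outcome cross-sectional points away from such a covariate.

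At stake is the smallest effect that 72 classes can detect. The article already plans the type of model that would do better, but only for secondary analyses.

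**Working it through.** **Inputs from section 2.3.** 36 classes of 25 per arm; cluster-size coefficient of variation (CV) 0.5; control proportion 5%; type I error 5% (taken as two-sided); power 90%; intra-class correlation (ICC) 0.02 to 0.2. **Assumed, not in the article:** a normal change score with equal SD in both arms, and a cut-off that gives the 5% control rate.

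**1. Reproduce the stated figure.** With m = 25 and L = m·ICC/(m·ICC + 1 − ICC), the design effect is [1 + (m − 1)·ICC] / [1 − CV²·L(1 − L)].
- ICC 0.02: L = 0.338, design effect 1.48/0.944 = 1.57, effective n per arm 900/1.57 ≈ 574.
- ICC 0.20: L = 0.862, design effect 5.80/0.970 = 5.98, effective n per arm 900/5.98 ≈ 151.

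Solving the pooled two-proportion test for 90% power from 5% gives differences of 5.04 and 11.49 points. These match the stated 5.0 and 11.5.

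**2. Express the binary effect as a shift in the score.** Shift = z(p₂) − z(0.05). For p₂ = 10.04% this is 0.365 SD; for p₂ = 16.49% it is 0.670 SD.

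**3. Continuous score, same ICC on both scales.** Detectable shift = (1.960 + 1.2816)·√(2/n) = 3.2415·√(2/n).
- n = 574: 0.191 SD, ratio 0.365/0.191 = 1.91, efficiency (0.191/0.365)² = 0.27.
- n = 151: 0.374 SD, ratio 0.670/0.374 = 1.79, efficiency (0.374/0.670)² = 0.31.

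The loss here is 69–73%, but section 2.3 gives its ICC in a calculation about a proportion. Cutting a normal score near its tail weakens the within-class correlation, so the score's own ICC must be larger than the flag's.

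**4. Carry the ICC consistently.** For a score ICC of ρ cut at proportion p, the flag's ICC is [Φ₂(z_p, z_p; ρ) − p²] / [p(1 − p)], where Φ₂ is the bivariate normal probability and p is taken as the mean of the two arms' proportions.

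| Starting point | Flag ICC | Score ICC | Binary shift (SD) | Continuous shift (SD) | Ratio | Loss, 1 − 1/ratio² |
|---|---|---|---|---|---|---|
| Protocol ICC read as the flag's | 0.02 | 0.065 | 0.365 | 0.252 | 1.45 | 53% |
| Protocol ICC read as the flag's | 0.20 | 0.417 | 0.670 | 0.510 | 1.31 | 42% |
| Protocol ICC read as the score's | 0.006 | 0.02 | 0.319 | 0.191 | 1.67 | 64% |
| Protocol ICC read as the score's | 0.075 | 0.20 | 0.489 | 0.374 | 1.31 | 42% |

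With the simpler design effect 1 + [(CV² + 1)m − 1]·ICC, the corresponding losses run from 37% to 63%.

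**5. Dependence on the cut-off.** Ignoring clustering, the efficiency of a cut at p is φ(z_p)²/[p(1 − p)]. The loss is 78% at p = 5%, 71% at 7.5%, 42% at 30% and 36% at 50%. The more common improvement is, the less the cut costs.

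**6. Gain from T0.** With equal variances and T0–T1 correlation r, a change score has variance 2σ²(1 − r) and the T0-adjusted T1 score has σ²(1 − r²). The ratio is (1 + r)/2: 0.80 at r = 0.6, and 0.65 to 0.90 for r from 0.3 to 0.8. This is a student-level calculation and r is an assumption.

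**The case against.** The strongest reply is that sections 2.3, 2.7.1 and 3.1 agree on a dichotomous primary outcome, that a responder proportion is legitimate and easy to read, and that the trial is correctly sized for it. All of that stands, so this is a better choice of method and not the correction of an error.

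Three stronger readings are tempting, and the article supports none of them.

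- **That about 70% of the information is lost and the detectable effect is twice as large as it need be.** With clustering, this requires the same ICC for the flag and the score. The article does not say so, and under the normal model a common ICC cannot hold.
- **That T0 is ignored.** Improvement can only be scored against an earlier measurement, so T0 enters through the endpoint. Section 3.1 is silent on covariates; a list may sit in an analysis plan that is not shown. What can be said is that no T0 covariate is stated.
- **That regression to the mean, ceiling effects or chance T0 differences bias the result.** Section 2.5 randomises classes within each school, balanced and with the same science teacher in both arms. These features act on both arms alike, and chance imbalance is random error. They cost precision only.

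The replacement also has open issues. The questionnaire is still being validated, don't-know answers are allowed, and the article does not say which of the 28 items load on the general factor. A flag built on the same score inherits these, so they do not favour the dichotomy.

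**Conclusion.** The point holds as one of efficiency. Under a normal change score, a 5% control rate and consistently carried ICCs, dichotomising loses roughly 40–64% of the information, and the detectable shift is about 1.3 to 1.7 times what the continuous score would allow. The loss is smaller if improvement is more common than 5%. T0 adjustment adds a further gain whose size rests on a correlation the article does not give. Validity is not in question and the stated power reproduces. This is an inexpensive improvement worth making, not a flaw that would invalidate the trial.

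**What to change.** Before any outcome is compared by arm:

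- Make the primary analysis the T1 sustainable-food score in a linear mixed model with arm, T0 score, and school and class terms. Report the adjusted mean difference with its 95% confidence interval, and name T1 as the primary time point.
- Keep the proportion improved, with a cut-off fixed in advance and adjustment for T0, as a supporting analysis.
- If the binary endpoint must stay primary, add the T0 score to its model and make the continuous analysis the key supporting one.
- Delete the description of the analysis as cross-sectional, and restate the detectable effect in SD units.

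No new data are needed. The cost is a documented, dated change to the primary analysis of a registered trial that has been recruiting since September 2022, and a headline result given as a mean difference instead of a percentage.

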### 3.2 Analysis of qualitative data

#### 3.2.1 Process analysis and elements of implementation

Interview data will be analyzed by QDA Miner. A coding framework will be developed between the Dijon and Montpellier teams, and a content analysis method will be applied. This method consists of identifying content referring to themes, i.e. units of meaning that can be isolated and analyzed in a cross-cutting way, indicators allowing the inference of knowledge relating to the conditions of reception / production (inferred variables) of these statements [75]. Content analysis "breaks down, as it were, the singularity of the discourse and cuts across what, from one interview to the next, refers to the same theme"; "the identification of themes and the construction of the analysis grid are carried out on the basis of the descriptive hypotheses of the research (…). Once selected for the analysis of a corpus, the themes constitute the stable framework for the analysis of all the interviews (…)" [76, *our translation*].

The themes of interest in the interview guide, as well as new themes found in the data, will be analyzed in order to contextualize everyone’s viewpoints and experiences. When analyzing and synthesizing the interviews and focus groups, a table will be drawn up with extracts of the most important findings from the qualitative research, as well as quotes from the interviews.

#### 3.2.2 Transferability analysis

Interview data will be analyzed in two steps: by inductive content analysis method and by a coding framework based on items guide and on data from the scientific literature.

## 4. Results

Recruitment began in September 2022 and will run until June 30, 2024. The 72 classes recruited will be followed over two school years. Different classes were recruited between the 2022–2023 and 2023–2024 school years.

Focus groups and qualitative interviews began in January 2024 and will continue until the end of June 2024

## 5. Discussion

Epidaure Market is a preventive initiative for science teachers, aimed at changing the motives for food choices among teenagers in the 5th and 4th grades. The school environment is an ideal place for the implementation of health-behavior interventions. Adolescents are already in the process of learning and changing their behavior. A multi-component approach (intervention carried out in the school curriculum and by teachers) and its theoretical underpinning (DEVA method, Ajzen’s TBP, BCTs) to guide intervention design enable behavior change. Existing interventions focus on obesity prevention, physical activity or the food environment. The main objective of this study is to evaluate the effectiveness of the intervention on food choice motives.

The existing intervention designed to change eating behaviors focused on the food environment [77], in particular through the influence of product availability and accessibility [78–80]. Our intervention take account the influence of the food environment via the choice of products in the virtual supermarket.

Furthermore, little is known about the psychosocial factors which influence the behavioral change produced by these interventions [15, 26]. Thanks to the originality of its design, its theoretical foundations and the combination of objective and self-reported evaluations of food choice motivation, the Epidaure Market study is expected to add to knowledge about the effectiveness of a multi-component intervention and the psychosocial mechanisms that underlie its impact.

The school environment is the ideal place for this type of intervention [27, 28], but it has its limits. Parents’ influence on teenagers’ diet is a key factor [81, 82], but it’s difficult to reach them with this type of intervention. On the other hand, food choice motives can play a mediating role between personal norms and values and eating behaviors [41, 42]. In addition, the constraints of class time limit the content of sessions and evaluation times, which can be impacted by the conditions of the school environment and access to computer tools. At last, Epidaure Market is an action that is carried out autonomously by science teachers. Its fidelity therefore depends on the teacher’s willingness and the way in which the teaching staff is supported in setting up and deploying the intervention.

In presenting the protocol for this randomized controlled trial, we emphasize the importance of designing and implementing this trial on sound theoretical foundations related to health behavior change. Moreover, by combining the evaluation of a second territory, a transferability assessment of the intervention can be carried out with a view to future deployment at French territory level. The qualitative study will enable us to identify the levers and obstacles linked to the acceptability of the intervention, as well as to its implementation, so that we can perfect the sessions and the video game to make it accessible to as many teachers and students as possible. In a broader perspective, there is a particular interest in assessing the effectiveness and transferability of the Epidaure Market intervention, especially regarding the issues related to PHIR (Population Health Intervention Research) and the deployment of evidence-based interventions in health promotion.
